## Abstract

**Background:**

Although electronic medication administration record systems have been implemented in settings where nurses work, nursing students commonly lack robust learning opportunities to practice the skills and workflow of digitalized medication administration during their formative education. As a result, nursing students’ performance in administering medication facilitated by technology is often poor. Serious gaming has been recommended as a possible intervention to improve nursing students’ performance with electronic medication administration in nursing education.

**Objective:**

The objectives of this study are to examine whether the use of a gamified electronic medication administration simulator (1) improves nursing students’ attention to medication administration safety within simulated practice, (2) increases student self-efficacy and knowledge of the medication administration process, and (3) improves motivational and cognitive processing attributes related to student learning in a technology-enabled environment.

**Methods:**

This study comprised the development of a gamified electronic medication administration record simulator and its evaluation in 2 phases. Phase 1 consists of a prospective, pragmatic randomized controlled trial with second-year baccalaureate nursing students at a Canadian university. Phase 2 consists of qualitative focus group interviews with a cross-section of nursing student participants.

**Results:**

The gamified medication administration simulator has been developed, and data collection is currently under way.

**Conclusions:**

If the gamified electronic medication administration simulator is found to be effective, it could be used to support other health professional simulated education and scaled more widely in nursing education programs.

**Trial Registration:**

ClinicalTrials.gov NCT03219151; https://clinicaltrials.gov/show/NCT03219151 (Archived by WebCite at http://www.webcitation.org/6yjBROoDt)

**Registered Report Identifier:**

RR1-10.2196/9601

## Introduction

### Background

Ensuring clinician sciences students have access to appropriate and pedagogically robust clinical learning opportunities is important to generate future cohorts of competent practitioners. The wide-scale adoption of high-fidelity patient simulation tools into clinical education (ie, nursing, medicine, and pharmacy) [1,2] is increasingly being extended and amplified through the use of technology-enabled (ie, online) serious gaming and other gamified approaches [3,4]. Serious gaming or gamification has been defined by Koch et al [5] as “the use of game design elements in nongame contexts” for the purposes of engaging learners in solving complex problems. In nursing education, there is currently minimal use of immersive, technology-enabled, or gamified approaches for students to practice clinical skills and judgment [6,7]. Commonly, in-person, simulated practice with high-fidelity patient simulation provides students the only functional opportunity to learn various clinical skills (eg, medication administration) before interacting with real patients in health care environments such as hospitals and in the community [7]. Although this type of in-person simulation has been found to be extremely effective toward generating clinical competency and skills [8,9], virtually all this kind of learning is contingent on the availability of, and access to, a physical simulation laboratory. Given the increasing enrollment sizes and current financial restraints present in many universities and colleges, scalable, cost-effective, and authentic [10] technology-enabled approaches (including gamification) for clinical nursing education are warranted.

### Electronic Medication Administration and Nursing Education

Electronic medication administration record (eMAR) systems have become more popular in many health care environments over the last decade, as a mechanism to improve medication safety. In brief, an eMAR system is a type of clinical technology that a health care provider (ie, nurse) uses to both validate and record the administration of medications. eMAR systems commonly use barcode technology to ensure that the correct medication is being administered to the correct patient at the correct time, dosage, and route [11]. Nurses are currently one of the largest user groups of eMAR technology [12,13]; therefore, it is essential that eMAR medication administration skills-building is fully embedded within nursing education. In clinical practice settings where eMAR systems are used effectively, statistically significant reductions in medication errors in comparison with those using paper-based medication administration processes have been reported [14]. Due to ongoing high rates of adverse medication events in both Canada and the United States [15,16], clinical technology such as eMARs may be essential for the reduction of medication-related errors [17,18].

One significant issue within nursing clinical education is competency and self-efficacy development in safe medication administration practices. Commonly, nursing students receive theoretical courses related to pharmacology and also clinically focused courses during the early years of their undergraduate education. Before students administering medications to real patients, learners usually participate in simulated, in-person learning opportunities within a laboratory setting. In these controlled learning environments, students can practice skills and further integrate their theoretical knowledge of pharmacology with professional practice skills related to medication administration. With recent advances in clinical technology such as eMAR systems [19], the complexity of the medication administration process has become a recognized nursing education and simulation issue [11,20-22]. Past research examining eMAR in nursing education simulation has outlined a range of factors limiting student success in this new modality of medication administration—namely, the amount of time and access students have to learn the unique workflows and clinical decision-making requirements in a digitized medication administration process [22]. There has been little research into whether serious gaming or gamification might be used as a tool to educate students in the complex tasks and processes inherent in medication administration [3,23], outside of the simulation laboratory. Finally, there are no known studies that examine whether medication administration gaming, in advance of simulated clinical practice, results in better nursing student learning, self-efficacy, and performance outcomes.

### Objectives of the Study

The main objectives of this study are to examine whether the use of an eMAR simulation serious game (1) improves nursing students’ attention to medication administration safety within simulated practice, (2) increases student self-efficacy and knowledge of the medication administration process, and (3) improves motivational (ie, attention, relevance, confidence, and satisfaction) and cognitive processing attributes (ie, invested mental effort and difficulty to learn game) related to student learning in a technology-enabled environment. Three specific research questions will be addressed in this study:

Does the use of an eMAR simulation game improve the eMAR medication administration safety for nursing students during in-person, simulated clinical practice?Does the use of an eMAR simulation game improve learner self-efficacy and knowledge toward eMAR medication administration processes in nursing students for in-person, simulated clinical practice?Does the use of an eMAR simulation game improve the motivational and cognitive processing attributes of nursing students regarding their learning of eMAR medication administration in a technology-enabled environment?

## Methods

### Development of a Prototype Electronic Medication Administration Record Simulation Game

At a large Canadian university in southern Ontario, a simulated eMAR system named the *SMART eMAR* was designed, developed, and implemented by faculty and students [24,25]. The SMART eMAR is used within the university’s clinical simulation laboratory (CSL) and provides students the opportunity to practice medication administration processes during various in-person, simulated clinical practicum courses. The SMART eMAR is a cost-effective, scalable, and customizable platform that resembles a real clinical eMAR system in terms of both interface and usability. The system contains all the major decision support elements and functionalities of a real eMAR system, including color-coded decision support related to incorrect barcode scans of medication or patient identification bracelets, barcode scanning capabilities of a host of inert medications used in the CSL, auto-populating data fields for time stamps and date, and qualitative text fields for nurse signatures or commenting. Both the hardware and software components of the SMART eMAR are mounted onto hospital-grade Ergotron mobile carts to replicate the usability and physical appearance of a clinical workstation on wheels.

First, although the SMART eMAR was designed to have a simplistic eMAR user interface (vs eMAR platforms found in acute care hospital environments), students had a difficult time learning how to effectively use and administer medications using this system [11]. Findings from this previous research also suggested that nursing students did not feel that they possessed enough knowledge regarding the process of electronic medication administration or the clinical judgment factors (ie, specific time-dose dependencies associated with some medications) to effectively use the SMART eMAR in simulated practice [11,20]. Second, students reported that they did not feel they had adequate time with the SMART eMAR to fully understand the work processes required to use the system confidently [11]. These findings are consistent with other research examining medication administration by nursing students [26]. Gamification of the eMAR process was selected by the research team to be both an innovative and logical solution to address the learning barriers currently faced by students [11].

To assist with game development of an eMAR simulation game, the research team partnered with a video game company (Mikutech, Joydrop Ltd, London, Canada) that has significant experience in the areas of video game and software development, including the specialized fields of education, engineering, and health care [27]. Drawing on previous research and medication administration workflow on the SMART eMAR [11,24], 2 main teaching-learning directions were targeted in the eMAR simulation game development. First, the main objective of the eMAR simulation game was to afford students a virtual and immersive opportunity to practice medication administration using an eMAR system in a structured environment that provides feedback consistent with previously published best practices [11,20,25]. Second, the simulation game was planned to gamify the medication administration process for a range of patient’s clinical presentations, with multiple feedback loops for each decision point along the medication administration pathway. Using a finite-state machine logic, each of these feedback loops could result in either *success, qualified success,* or *failure* in the administration process, which would be reported back to the student upon their completion of the medication administration event. As medication errors are commonly generated through a range of dynamic procedural, clinical decision-making, and human and environmental factors [28], the game was designed to be as expansive as possible for students to generate eMAR-enabled errors of all complexions, including incorrect medication dosage interpretation, administration timing, clinical indication and appropriateness, and other best practice processes deviations (eg, failure to wash hands before administration, failing to barcode scan the patient identification band or medication barcode, and failing to complete a vital signs assessment before administering an antihypertensive medication). If a student failed to attend to a specific medication administration best practice and further dependent on the severity of the error, feedback would be provided to the student on completion of the scenario, informing them of the number of errors made and brief rationale related to the mechanism of the error(s) themselves. Figure 1 provides a screenshot of an element of the game user interface, along with various manipulable objects that can spawn specific information (ie, drop-down menu to select a specific patient medication error, vital signs machine, patient dialogue, handwashing, scanning of barcodes, etc) related to the patient scenario and the medication administration context.

### Study Design

The primary study design (phase 1) will consist of a prospective, 2-armed pragmatic randomized controlled trial. Phase 2 will consist of qualitative focus group interviews, conducted after the completion of phase 1.

### Setting and Recruitment of Participants

Two waves of second-year baccalaureate nursing student participants will be contacted and recruited for participation in this proposed study at the beginning of 2 separate academic semesters: wave 1 will commence in September 2017 (fall semester) and wave 2 in January 2018 (winter semester). Due to the size of the second-year nursing student cohort (N=150) and resource limitations of the CSL, only half (n=75) of the students will partake in simulated clinical education in the CSL, per semester (split between fall and winter). Inclusion criteria for this study will be (1) second-year nursing students and (2) partaking in clinical simulated education either in fall 2017 or winter 2018 semesters. Students recruited in this study will not have had previous exposure to medication administration, and this simulated clinical experience will be their first formative interaction with medication administration and the SMART eMAR.

**Figure 1 figure1:**
[figure not shown]
Screenshot of the electronic medication administration record (eMAR) simulation game’s user interface and various player-manipulable objects.

Before the start of each term, a researcher-led presentation will be delivered outlining the proposed study purpose, methods, and study benefits. Given the typical student enrollment within second year of the BScN program, it is expected that approximately 150 students will fit this inclusion criterion and be eligible for recruitment into the study. Participants will be offered a Can $5 gift card for a coffee shop as a nominal incentive to participate in the study. Due to the high recruitment success rate experienced in the corresponding pilot study completed in April 2016 (25/27, 93% of students sampled) [11], we estimate 120 participants will be recruited. By including at least 120 participants, phase 1 of our study will be able to detect an intervention effect size of 0.25, with a power of 0.8 and a .05 level of significance, based on a 2-tailed *t* test analysis, as calculated by G*Power 3.1 (Heinrich-Heine-Universität Düsseldorf, Germany).

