### Strengths and Limitations

As a strength, this study will be one of the first appropriately powered trials of a serious gaming intervention in nursing education. Furthermore, the pragmatic randomized controlled trial design [46] with complementing qualitative elements will assist in generating informative insights related to the effectiveness of using a serious gaming intervention to educate students to the complexities of medication administration in an eMAR environment. Although this study has some strengths, there are some limitations that should be outlined. First, the observational method and environment for data collection raise the potential of an observer effect, in that participants may recognize they are being observed by members of the research team during their return demonstration of a medication administration scenario in the CSL. Second, the variability in data collection by multiple observers may be a potential limitation. Although standardized observation guides and training will be provided to the data collectors, interrater reliability between observers may be a source of study error. Finally, given the structure of the game, it is not possible to fully ascertain whether there is a dose-response relationship between cumulative gameplay time and its effect on medication error frequency rates. As the eMAR simulation game offers the player a fair amount of autonomy to make errors and experiment with different actions and processes, any linear relationship examined between overall gameplay time of a participant and their medication error rate may not be an accurate depiction of medication administration knowledge or comprehension.

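### The 80% power claim for an effect size of 0.25 names no metric; read as a standardised mean difference, power with 120 students is about 27%, and 80% is reached only at d = 0.52

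*Protocol article*

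**What the plan says.** The article has one sample size statement, in the last paragraph of Setting and Recruitment of Participants. For a sample of 120 or more, it claims that "phase 1 of our study will be able to detect an intervention effect size of 0.25, with a power of 0.8". The test behind the claim is a two-sided t test at the 5% level, and G*Power 3.1 is named as the software. No effect-size metric, standard deviation, raw difference, outcome, type of t test or G*Power procedure is attached to the 0.25.

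Study Design sets two randomised arms, and Data Collection (Phase 1) sets a 1:1 ratio by simple randomisation, so about 60 students per arm are expected. Strengths and Limitations then says that "this study will be one of the first appropriately powered trials of a serious gaming intervention in nursing education".

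**The concern.** An effect size given without a label for a t test in a two-arm trial will normally be read as the difference in means divided by the standard deviation. On that scale, 60 per arm is far too few for 80% power at 0.25. The gap is too large to come from rounding or from the choice of software.

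Two things depend on the sentence. The claim of appropriate power has no other support in the article. In addition, a reader who takes 0.25 as d could treat a null result as evidence against a quarter-SD benefit, although the trial would miss a true effect of that size about 73% of the time (1 − 0.274).

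**Working it through.** **Inputs.** N = 120, effect size 0.25, power 0.80, two-sided alpha .05, t test (Setting and Recruitment of Participants); two arms (Study Design); 1:1 allocation (Data Collection, Phase 1). Hence n = 60 per arm. This assumes an even split and no dropout; the article states no dropout allowance.

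**1. Trying to reproduce the stated 80%.** Power comes from the noncentral t distribution, with noncentrality δ as shown.

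| Reading of 0.25 | δ | Power at N = 120 |
|---|---|---|
| d, independent samples, 60 vs 60 | 0.25 × √(60×60/120) = 1.369 | 0.274 |
| Same, one-sided | 1.369 | 0.388 |
| d, with 120 in each arm | 0.25 × √60 = 1.936 | 0.488 |
| Paired dz, one arm of 60 | 0.25 × √60 = 1.936 | 0.478 |
| Paired dz, all 120 pooled | 0.25 × √120 = 2.739 | 0.775 (needs 128) |
| Cohen's f (equals d = 0.50) | √(0.25² × 120) = 2.739 | 0.775 (needs 128) |
| Point-biserial r | √(120 × 0.0625/0.9375) = √8 = 2.828 | 0.801 |

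Only the last row reproduces the claim. It does so exactly: power is 0.798 at N = 119 and 0.801 at N = 120, so 120 is the smallest sample that reaches 80%.

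**2. What that correlation means as a mean difference.** With equal arms, d = 2r/√(1 − r²) = 0.50/√0.9375 = 0.516.

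**3. Detectable difference with 60 per arm.** Solving the independent-samples power equation for 0.80 gives d = 0.516, which agrees with step 2 to three decimals.

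**4. Sample size if d = 0.25 were the target.** 252 per arm give 0.7998; 253 per arm are needed, so 506 in total (252 per arm by the normal approximation).

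**5. Sensitivity to the assumptions.** A 50/70 split, possible under simple randomisation, lowers power at d = 0.25 from 27.4% to 26.8%. A between-arm test on change scores would come close to 80% at d = 0.25 only with a pre-post correlation of about 0.88 (power 0.792). The article gives no such correlation. Its Outcomes section describes the checklist measures (deviations, errors or near misses, time) as observed at the return demonstration only, so no baseline is described for them.

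**6. Precision of a null result.** In SD units the 95% interval half-width is about 1.98 × √(2/60) = 0.36. An observed difference of zero would not exclude 0.25 SD.

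**The case against.** The strongest defence is that the sentence never says d. With 0.25 as a point-biserial correlation, a two-tailed, two-group t test gives the stated N, alpha and power, with 120 as the exact minimum. The calculation may have been run correctly and only the label lost. This stands, with two limits. The article does not mention a correlation, so the reading is inferred from a numerical match; and 120 is also the number the investigators expected to recruit, so part of the match could be chance.

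A reader might therefore infer that the power calculation is an outright arithmetic error. The article does not support so flat a statement, because the metric and the G*Power procedure are not given. A reader might also infer that the trial is too small and needs about 506 students. That does not follow either, since nothing in the article shows that a quarter-SD difference was the intended target.

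The defence does not remove the need for a correction. An unlabelled correlation, printed where readers expect d, misleads them by the same factor of about two. Nor is this a detail left to a fuller document: the article prints a specific power claim and builds a stated strength on it.

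**Conclusion.** The point holds conditionally. If 0.25 is a standardised mean difference, the stated 80% power is wrong: it is about 27%, and the difference detectable with 80% power is 0.516 SD, about twice the printed value. If 0.25 is a point-biserial correlation, the power is right but the scale is missing, and the detectable difference is again 0.516 SD. The paired and Cohen's f readings reach at most 0.775 and do not reproduce the claim.

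The practical conclusion is the same on both main readings: 120 students in two equal arms give 80% power for a between-arm difference of about half an SD. This rests on 60 analysed per arm, an independent-samples t test and two-sided alpha .05; imbalance or dropout would lower the sensitivity slightly.

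**What to change.** Replace the power sentence with wording such as: *120 participants (60 per arm) give 80% power to detect a standardised between-group difference of d = 0.52 (two-sided independent-samples t test, alpha .05); power for d = 0.25 is about 27%.* If a correlation was the input, add: *equivalent to a point-biserial r = 0.25*. The G*Power record should settle which it was.

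Under Strengths and Limitations, qualify the power claim as applying to moderate differences of about half an SD.

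The cost is wording only. Design, enrolment and analysis are unchanged, and the replacement is accurate whichever metric was used. The one drawback is that the stated detectable effect looks less favourable than the printed 0.25.

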### Data Collection

#### Phase 1

After recruitment and enrollment into the study (week 1), nursing students in each semester will be randomized into either the intervention or control group and will be assigned a unique participant code number. The allocation ratio will be 1:1 (intervention or control group), following a simple randomization procedure (Microsoft Excel [Microsoft Corp.] random number table). Research team members involved in data collection will be blinded to the allocation; participants will become aware of their randomization on receipt of an email from the researchers outlining their allocation into the intervention or control group. At this time, students in the intervention group will receive access to the eMAR simulation game approximately 2 weeks in advance of their in-person simulation sessions with the eMAR technology in the CSL. Along with access to the eMAR simulation game, students in the intervention group will also have access to other usual preparatory educational resources related to medication administration, such as a video demonstrating proper administration technique and a PowerPoint presentation on eMAR medication administration. To ensure a consistent duration of game intervention, students will be requested to use the eMAR simulation game for a minimum of 60 min (with no maximum) [29] before conducting their return demonstration of a medication administration using the actual SMART eMAR system in the CSL (starting week 5); analytics software operating in the background of the game will be used to track the average game play duration of participants. Students allocated to the control group will receive the usual preparatory resources related to eMAR medication administration, without access to the eMAR simulation game. At the conclusion of the trial in late October and February (week 9), all participants in the control group will receive access to the eMAR simulation game.

The duration of the active trial in each academic semester will be approximately 4 weeks, running the months of October and February. The simulated return-demonstration patient scenario that all students will be required to complete involves conducting a baseline physical assessment on a high-fidelity human mannequin simulator, performing the ordered medication administration using the SMART eMAR system, and conducting a patient follow-up assessment and documentation of the encounter in the patient’s clinical record. All participants in the intervention and control groups will receive the same patient and medication administration scenario to maximize contextual internal validity.

Prepost data related to medication self-efficacy and knowledge will be collected through a Qualtrics (Qualtrics Inc.) Web-based survey platform before (week 4) and after the simulated return-demonstration patient scenario (week 8). Cross-sectional survey data will be collected from the intervention group only, immediately after the simulated return-demonstration patient scenario (week 8; Figure 2).

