#### Outcomes

Data will be collected by 4 data collectors (nursing graduate students with clinical backgrounds using eMAR technology) who will observe nursing student participants during their return demonstration of medication administration using the SMART eMAR (weeks 5-8). These data collectors will be trained by members of the research team before the study initiation to ensure the appropriate and consistent use of the checklist to collect participant data. Mock student return demonstrations and related data collection will be conducted to improve interrater reliability; Fleiss kappa coefficients will be calculated and used to further refine interrater reliability of the data collection procedure. A formalized checklist that has been developed and used previously in an adapted form by the research team [20] will be implemented as the primary data collection instrument for phase 1. This data collection checklist will capture the following quantitative data during each participant’s medication administration return demonstration using the SMART eMAR: (1) frequency of deviations from medication administration best practices, (2) number of actual medication errors or near misses generated by the student that violate the various medication best practices and provincial regulatory requirements related to medication administration [30,31], and (3) overall duration of time required by the student to complete the entire medication administration simulated scenario. Secondary outcomes using prepost survey data related to medication self-efficacy and knowledge will be collected using questions modified from previously developed and tested instruments [32,33]. Secondary outcome cross-sectional data will also be collected using questions modified from the Huang et al’s [34] validated instrument that measures motivational (ie, attention, relevance, confidence, satisfaction) and cognitive processing of learning in game-based environments (20 questions, Cronbach alpha=.91). Measurement of motivational and cognitive processes of learning will identify levels of participant motivation related to cognitive load requirements demanded by the eMAR simulation game.

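### The planned Student t test leaves any semester or observer variance in the error term; adjusting for both is a cheap gain in precision (minor)

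*Protocol article*

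**What the plan says.** **Allocation.** Two waves are recruited, fall 2017 and winter 2018, with about 75 eligible students in each (Setting and Recruitment of Participants). Data Collection, Phase 1 says that "nursing students in each semester will be randomized into either the intervention or control group", in a 1:1 ratio, "following a simple randomization procedure".

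**Measurement.** Under Outcomes, "Data will be collected by 4 data collectors"; these are trained graduate nurses using a checklist. Data Collection, Phase 1 has the research staff who collect data blinded to arm. Outcomes adds mock demonstrations and Fleiss kappa to improve agreement. Strengths and Limitations adds standardised observation guides and still concedes that "the variability in data collection by multiple observers may be a potential limitation".

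**Analysis.** Data Analysis, Phase 1 names a Student t test for medication errors or near misses, deviations from best practice, and time taken. No semester or observer term appears. The sample size is "based on a 2-tailed *t* test analysis" as well: the trial is said to "detect an intervention effect size of 0.25" "with a power of 0.8 and a .05 level of significance", and "we estimate 120 participants will be recruited".

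**The concern.** Semester is part of the design, because each wave is randomised on its own. Observer is a source of variation that the article itself raises. Both can be put in a model, and a two-sample t test can carry neither. If students in the two semesters differ on average, or if observers differ in strictness, that variation inflates the residual variance and widens the confidence interval for the game's effect.

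The trial cannot readily buy this precision back with more students, since the whole second-year cohort is about 150. What is at stake is some power and a narrower interval. The correctness of the comparison is not at stake.

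**Working it through.** **Inputs from the article.** N = 120, taken as 60 per arm; two-sided alpha 0.05; power 0.80; effect size 0.25 with no metric named; two semesters; four observers. Data Analysis describes the comparison in pre/post terms, although these outcomes are observed at the return demonstration; I read it as a comparison between arms.

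**Inputs assumed.** R², the share of within-arm outcome variance due to semester plus observer, is not in the documents. I take 0 to 0.30. I also assume one observer per student, which the article does not state.

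**Step 1: the plan's own figure.** For a two-sample t test the noncentrality is d × √(N/4), with N − 2 = 118 degrees of freedom.

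- If 0.25 is a standardised mean difference: 0.25 × √30 = 1.369, power 0.274. This does not reproduce 0.80.
- If 0.25 is a point-biserial correlation: d = 2 × 0.25 / √(1 − 0.0625) = 0.516; 0.516 × √30 = 2.828, power 0.801. N = 120 is the smallest total reaching 0.80 (119 gives 0.798).

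Only the correlation reading, of those tried, has N = 120 as the smallest sufficient total, so d = 0.516 is the working effect.

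**Step 2: adjusted model.** One semester indicator and three observer indicators leave 120 − 6 = 114 degrees of freedom. The noncentrality becomes d × √30 / √(1 − R²), if arms are balanced over both factors.

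| R² | Noncentrality at d = 0.516 | Power, adjusted | d detectable with 80% power |
|---|---|---|---|
| 0 | 2.828 | 0.801 | 0.516 |
| 0.05 | 2.902 | 0.821 | 0.503 |
| 0.10 | 2.981 | 0.840 | 0.489 |
| 0.20 | 3.162 | 0.880 | 0.461 |
| 0.30 | 3.381 | 0.918 | 0.432 |

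**Step 3: simulation under simple randomisation.** Two waves of 60, observers assigned at random, variance split equally between semester and observer, 10,000 runs per setting.

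| R² | Type I error, t test / adjusted | Power at d = 0.516, t test / adjusted |
|---|---|---|
| 0 | 0.052 / 0.053 | 0.797 / 0.784 |
| 0.10 | 0.049 / 0.048 | 0.798 / 0.822 |
| 0.20 | 0.049 / 0.050 | 0.799 / 0.865 |
| 0.30 | 0.050 / 0.051 | 0.796 / 0.906 |

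Both tests hold 5%. Adjusted power is 1 to 2 points below Step 2 because arm is correlated by chance with the four indicators. On average they take up 4/119 = 3.4% of the information on arm: 2.828 × √(1 − 0.034) = 2.780, power 0.787 at R² = 0. That explains the 1-point cost; the four lost degrees of freedom alone cost almost nothing (0.801 in Step 2).

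**Step 4: the other reading of 0.25.** At d = 0.25, adjusted power is 0.298, 0.329 and 0.368 for R² of 0.10, 0.20 and 0.30. Reaching 0.80 would need R² of about 0.77.

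**Step 5: uneven splits.** With 60 in a wave, simple randomisation gives a split of 36:24 or worse with probability 0.155. Yet 36:24 in both waves, the same way round, is 72:48 overall; at d = 0.5 that lowers power only from 0.775 to 0.758.

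**The case against.** The strongest reply is that nothing here is an error. The t test is valid under this randomisation, as Step 3 confirms. Covariate terms are commonly left to an analysis plan, which is not shown, and the article does not exclude an adjusted analysis. All of this stands as a limit on severity. It does not remove the point, because the article names a specific test, uses it for sizing too, and itself names a source of error which that test cannot use.

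The documents do not support several stronger readings that a reader might infer:

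- **Bias.** An uneven spread of arms over observers does move the estimate in a given trial, but that is chance variation already covered by the standard error. Bias would need observer assignment to depend on arm. The observers are blinded and nothing links them to arm.
- **Known variance.** Observer variation is acknowledged only as possible, and a semester effect is mentioned nowhere. Both waves come from the same cohort and receive the same scenario, so R² may be small.
- **Nothing done beyond training.** The article also specifies a checklist, mock demonstrations, Fleiss kappa and observation guides.
- **One recorded observer per student.** Neither the number of observers per student nor the recording of their identity is stated.
- **Faulty randomisation.** Simple randomisation is legitimate, and a 1:1 ratio does not promise equal counts. Step 5 shows how little the imbalance costs.

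**Conclusion.** The point holds as a minor matter of efficiency. The named t test forgoes precision that the design makes available, without harm to validity or type I error.

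At d of about 0.52 the gain from adjusting is about 2, 4 or 8 points of power for assumed variance shares of 5%, 10% or 20%. Under simple randomisation, the simulated gain is about 2 points at 10% and 7 at 20%. The downside is about 1 point if the factors explain nothing. These sizes rest on the assumed R², on one observer per student, and on 120 students with outcome data.

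A reader might hope that adjustment secures the trial's power. It does so only if 0.25 is a correlation. If it is a standardised mean difference, power stays between 0.27 and 0.37 for R² up to 0.30. The unnamed effect-size metric is then the larger problem, and a separate one.

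**What to change.** Before the arms are compared, replace the t test for errors or near misses, deviations and time with a linear model of each outcome on arm and semester. Add data collector as a fixed effect where the observer's identity was recorded. If it was not recorded in wave 1, record it in wave 2. Report the adjusted difference between arms with its 95% confidence interval. The Results section says that fall data collection has ended, so date the change and state whether any comparison by arm had already been made.

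The cost is one regression per outcome in place of a t test, four degrees of freedom, and possibly one extra field on the checklist.

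Optional, and only if wave 2 is not yet allocated: because students are enrolled before allocation, shuffle the enrolled list and split it in half for an exact 1:1 division, and spread both arms evenly over the data collectors. Someone other than the data collectors should do the scheduling, so that they stay blinded. The gain is small.
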